** *Qualitative* **			
Attitudes and beliefs	Relevant qualitative factors ECP	Semi structured interview	Researchers
	Relevant qualitative factors nurse	Semi structured interview	Researchers

Psychotropic drug use (PDU), Anatomical Therapeutical Chemical (ATC), Neuropsychiatric Inventory- Questionnaire (NPI-Q), Cohen-Mansfield Aggression Inventory (CMAI), Approaches to Dementia Questionnaire (ADQ), Elderly Care Physician (ECP), Competing Values Framework Scale (CVFS), Strain in dementia Care (SDC), the Maastricht Work Satisfaction Scale for Healthcare ’Maastrichtse Arbeidssatisfactie Schaal voor de Gezondheiszorg’ (MAS-GZ), Therapeutic Environment Screening Survey for Nursing Homes (TESS-NH).

### Data analysis

Quantitative (descriptive and multivariate) and qualitative analyses will be performed. For quantitative data analysis a multilevel model is built to investigate the potential associations with the frequency of PDU and with the appropriateness of PDU, taken into account that appropriateness of PDU is nested within DSCUs.

Data collection and analysis of the qualitative semi-structured interviews will be conducted as an iterative process with saturation as a guiding principle [51], implying interviews will be carried out until knowledge saturation is reached. This is known as the constant comparative method, which is part of the grounded theory approach [51].

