## Background

In the Netherlands approximately 37.000 patients with dementia reside in Dementia Special Care Units (DSCUs) of nursing homes [1,2]. The prevalence of neuropsychiatric symptoms (NPS) associated with dementia is high, more than 80% [3], and frequently a reason for prescription of psychotropic drugs (PDs) [4-6]. However, psychosocial interventions and restraints are also commonly used in the management of NPS [7]. Psychotropic drug use (PDU) rates in institutionalized patients with dementia vary from 63%-75% [6,8,9]. It is also known that antipsychotic use varies among countries between 11% and 52% [6,10-12].

PDs have considerable side effects. Antipsychotics are associated with increased occurrence of extrapyramidal symptoms, somnolence, increased risk for stroke and pneumonia and higher mortality rates [13-15]. Anxiolytic and hypnotic drugs are associated with falls [16]. PDs in general [17] and antipsychotics in particular also have negative effects on quality of life [18].

Long-term or inappropriate use of antipsychotics is common [19], a recent study found that 31% of the nursing home patients used PDs for a sustained period of at least 2 years [9] and in another study 74% of dementia patients in nursing homes used PDs for 83% of their nursing home stay [20]. This does not comply with available evidence on risks, side effects, limited evidence for efficacy of these drugs and long-term inefficacy [15,21,22]. That is why guidelines emphasize the restricted, short-term use and thus the appropriateness of PDU [23].

PDU varies considerably among nursing homes and DSCUs [24,25]. This could partly be explained by different prevalence rates of NPS among patients on DSCUs [3]. However there is growing evidence that this inter-DSCU variation in PDU is not only related to the severity of patients’ NPS [6,26]. The PDU variation is also related to drug prescription policies of the Elderly Care Physician (ECP) [5], staff distress/workload [26], physical environmental factors [25], and the bed capacity of the nursing home [27] (see Figure 1).

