## Methods/Design

### Design and eligibility

This study, the PROPER I study (PRescription Optimization of Psychotropic drugs in Elderly nuRsing home patients with dementia) is a cross-sectional mixed methods study and will be followed by the PROPER II study [28], a multi-center cluster randomized controlled, pragmatic trial on the efficacy of structured repeated multidisciplinary review on psychotropic drugs. The eligibility of nursing homes is based on a survey among ECPs working in nursing homes that we will carry out among all members of Verenso, the Dutch association of ECPs and community geriatricians. ECPs will be asked to count the number of patients, living on the DSCU they are responsible for, that receive one or more PDs. Nursing homes will be eligible if their ECPs fill in the survey about PDU for at least 3 DSCUs.

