### Study population and recruitment

According to our calculations (see section on Sample size), 36 DSCUs need to be recruited. Based on the results of the survey, 36 DSCUs will be divided over six nursing homes with high and six with low DSCU overall PDU rates. DSCUs with medium rates will be accepted if the nursing home’s overall rate is high or low on average; at least two out of three DSCUs need to score high or low within a nursing home. With this selection method the contrast in PDU among nursing homes is increased, which could facilitate finding relevant parameters of PDU, without loss of statistical dispersion for our analyses. No geographical considerations will be made in the recruitment process.

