### Quantitative measures

#### Frequency and appropriateness of PDU, primary outcome

PDU will be classified using the Anatomical Therapeutical Chemical (ATC) classification [29] and grouped into antipsychotics, anxiolytics, hypnotics, antidepressants, anticonvulsants and anti-dementia drugs.

For determining appropriateness of psychotropic drug use a screening tool will be developed, based on the Medication Appropriateness Index (MAI). The MAI was developed in 1992 [30] to determine the drug’s appropriateness for individual patients on 10 items and is proven to be reliable [31] and applicable in the Dutch nursing home setting [32]. However, the MAI is not specifically developed as a tool to screen medical files for appropriateness of prescription of individual psychotropic drugs in dementia and thus does not sufficiently suit the needs for this study. We will therefore adapt the original MAI and develop an instrument that screens medical files for appropriateness of psychotropic drug prescription in dementia. The instrument will primarily screen PDs based on the Dutch association of ECP and community geriatricians (Verenso) guideline for problem behavior [23]. The instrument will also include information about interactions and contraindications that originates from the database of the Royal Dutch Association for the advancement of Pharmacy (KNMP) [33]. PD information that is not provided by the Dutch Verenso guideline, will be derived from ‘Farmacotherapeutisch Kompas’ [34], published by the Dutch Health Care Insurance Board (CVZ) and based on the summary of product characteristics (SPC) [35]. Items will be weighted by an expert panel of pharmacists and ECPs who categorize the relative contribution of each item to the level of drug appropriateness.

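### The multilevel model names only DSCU nesting, although DSCUs are sampled within 12 nursing homes chosen on psychotropic drug use; standard errors for home-shared factors would be too small

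*Protocol article*

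**What the plan says.** Data analysis announces a multilevel model for associations with both frequency and appropriateness of PDU. It states one nesting, "taken into account that appropriateness of PDU is nested within DSCUs", and attaches it to appropriateness. No nursing-home level appears in the analysis text.

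The design sections make the home the unit of eligibility and selection:

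- Design and eligibility: "Nursing homes will be eligible if their ECPs fill in the survey about PDU for at least 3 DSCUs".
- Study population and recruitment: "36 DSCUs will be divided over six nursing homes with high and six with low DSCU overall PDU rates", with the condition that "at least two out of three DSCUs need to score high or low within a nursing home". The stated purpose is that "With this selection method the contrast in PDU among nursing homes is increased".
- Sample size: 540 patients in 36 DSCUs of twelve homes, on average 15 patients per DSCU.

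The Background says that "PDU varies considerably among nursing homes and DSCUs". Among factors related to this variation it lists "the bed capacity of the nursing home", and the conceptual framework gives nursing home characteristics as an example of the physical environment.

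**The concern.** A DSCU random intercept absorbs the correlation among patients of one unit. It does not absorb correlation among the three units of one home. If homes differ, a factor that takes a single value per home has 12 independent values, yet the model credits it with 36.

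For frequency, homes differ by construction, because they are picked from the high and low ends and most of a home's units must agree in direction. At stake are false-positive associations for home-shared characteristics, in a study whose aim is to find physician and environmental factors behind PDU.

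**Working it through.** **The plan's own figures.** 360 / 0.67 = 537.3, or exactly 540 with two thirds in place of 0.67. 36 x 15 = 540 and 36 / 12 = 3 DSCUs per home. The recruitment figure reproduces and is not in question.

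**Inputs.** From Sample size: k = 3 DSCUs per home, m = 15 patients per DSCU, 12 homes. Assumed, because the documents do not give them: total ICC 0.05 to 0.20, home share of the cluster variance 0 to 100%, two-sided alpha 0.05, a balanced design and a normal outcome. Total variance is set to 1, split into Vh (home), Vd (DSCU) and Ve (patient).

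**Standard error of a home-constant factor.** The variance of a home mean is:

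- true: Vh + Vd/3 + Ve/45
- under DSCU-only nesting: (Vh + Vd)/3 + Ve/45

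Example with ICC 0.10 and home share 50% (Vh = Vd = 0.05, Ve = 0.90): true 0.05 + 0.0167 + 0.02 = 0.0867; DSCU-only 0.0333 + 0.02 = 0.0533; SE ratio sqrt(0.0867 / 0.0533) = 1.275.

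Each cell gives the SE ratio, then the simulated rejection rate for a null home-constant covariate. The simulation regressed 36 DSCU means on the covariate, 6,000 runs per cell.

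| Home share | ICC 0.05 | ICC 0.10 | ICC 0.20 |
|---|---|---|---|
| 0% | 1.000; 4.8% | 1.000; 4.7% | 1.000; 5.1% |
| 25% | 1.105; 8.4% | 1.146; 8.3% | 1.181; 10.0% |
| 50% | 1.200; 9.9% | 1.275; 12.7% | 1.338; 14.6% |
| 75% | 1.289; 14.3% | 1.392; 16.1% | 1.478; 19.8% |
| 100% | 1.372; 16.5% | 1.500; 20.8% | 1.606; 25.2% |

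Regression on the 12 home means rejected in 4.7 to 5.5% in every cell. If only drug users are analysed, about 10 per DSCU (540 x 0.67 / 36), the ratio for shares of 25 to 100% runs from 1.083 to 1.558.

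**Partly shared factors.** With r the correlation between DSCU means of one home and c the within-home correlation of the covariate, the ratio is sqrt(1 + 2rc). At ICC 0.10 and share 50%, r = 0.05 / (0.10 + 0.90/15) = 0.3125. Then c = 1 gives 1.275, c = 0.5 gives sqrt(1.3125) = 1.15, and c = 0 gives 1.00.

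**Effect of selection on frequency.** Starting from ICC 0.10 and a 50% home share, the six highest and six lowest homes were taken on a noisy survey rate. The home share of cluster variance rose to about 72%, 77% and 82% with 36, 60 and 120 candidate homes. Taking the most extreme homes is an assumption; the protocol says high and low and accepts some medium-rate DSCUs.

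**Check with a binary outcome.** This simulation used 67% users, home and DSCU SDs of 0.3 to 0.5 on the logit scale, 60 candidate homes and selection on a separate survey draw. For a home-constant covariate, DSCU-level analysis rejected in 8 to 15% (random homes), 10 to 18% (outer tertiles) and 15 to 23% (six most extreme each side). With a within-home covariate correlation of 0.3 to 0.5 the rates were 5 to 9%, 6 to 11% and 8 to 13%.

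**The case against.** The strongest reply is that one sentence in a journal article names a DSCU level without excluding a home level, and that random-effect structure is normally settled in a fuller plan. It is true that nothing is excluded. But the sentence does state a structure, and that structure does not match the sampling described in the same article. An analyst who follows it obtains intervals that are too narrow for home-shared factors.

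The other replies limit the reach of the point, and these stand:

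- Most listed measures are at patient, nurse or DSCU level. The section on the physical environment lists unit-level items and no home-level measure; bed capacity appears only as background. Organizational culture is measured through individual nurses.
- A reader might infer that one elderly care physician (ECP) covers several DSCUs of a home, so that all ECP factors suffer in full. The documents do not say how many DSCUs an ECP covers. ECP factors are affected only as far as ECPs are shared or alike within a home.
- A reader might infer from the aim to "screen medical files for appropriateness of prescription of individual psychotropic drugs in dementia" that several scores per patient enter the model and need a patient level. That phrase describes what the existing index was not built for. Table 1 lists appropriateness at patient level, and the sample size counts drug-using patients. A drug level matters only if drug-level scores are modelled.
- Homes are selected on frequency, so selection-inflated figures do not carry over to appropriateness.
- The study is exploratory and sets no alpha. The 5% level here is illustrative.

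**Conclusion.** The point holds in a limited form. The stated nesting leaves out the level at which units are selected. For factors constant or strongly alike within a home, the DSCU-only standard error is too small whenever between-home variance is above zero. The true value is about 1.1 to 1.6 times as large, and type I error for a home-constant factor is roughly 8 to 25% at a nominal 5%. Both ranges rest on the assumed ICC of 0.05 to 0.20 and home share of 25 to 100%. The error is smaller for partly shared factors and absent for factors that vary independently between DSCUs, or if home variance is zero.

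A reader might conclude that all physician and environmental associations will be false-positive prone, or that error rates above 20% are to be expected. The documents support neither: the first ignores the level at which most factors are measured, and the second needs a large home variance or the most extreme selection of homes.

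**What to change.** Replace the nesting clause in Data analysis by a statement that, for both frequency and appropriateness, patients are nested in DSCUs and DSCUs in nursing homes, with random intercepts for home and DSCU. Add that home-level factors are judged with small-sample inference suited to 12 homes, using a method that fits the outcome type. An analysis of home means, with 12 - 2 = 10 degrees of freedom for one factor, is a simple check; it is the version simulated above, whereas the full mixed model was not simulated.

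An ECP identifier is needed only if ECPs cover more than one DSCU, and a patient intercept only if drug-level scores are modelled.

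The cost is a changed sentence, one more random effect and wider intervals for home-shared factors. Recruitment is unchanged. A home intercept does not cure distortion from selecting homes on the outcome, which is a separate matter.

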### Sample size

According to the n/10 rule [52,53] 360 patients are sufficient to study the number of variables needed for this study. 67% of the patients are expected to use PDs, which means that in total 540 patients need to be recruited. Regarding good sampling and an average cluster size of 15 patients per DSCU, 36 DSCUs of twelve different nursing homes will be recruited.

### Ethical approval

The study is undertaken in accordance with the declaration of Helsinki and will be carried out in accordance with the applicable rules in the Netherlands. According to the Medical Ethics Committee of the region Arnhem-Nijmegen, the Netherlands, the study does not need to be conducted according to the Medical Research Involving Human Subjects Act (WMO), because patients will not be directly involved. Relatives, if not available other representatives, of patients will be informed and asked if they object to the collection of data. If the relatives or representatives object, patients will be excluded from the data collection.

## Discussion

The high rates of long-term PDU [9] in combination with the risk of major and hazardous side effects, limited evidence for efficacy, long-term inefficacy [15,21,22] and guidelines recommending to regularly evaluate PDU [23], make it crucial to study PDU appropriateness and its associations.

It is hypothesized that the frequency as well as appropriateness of PDU varies between DSCUs, because of factors related to patient, ECP, nurse and physical environment, as described in a conceptual framework (Figure 1). More specifically, it is expected that factors like workload and staff distress influence the appropriateness of PDU.

A strength of this study is that the recruitment focuses on nursing homes/ DSCUs with low versus those with high PDU. Knowledge about extreme, i.e. low or high, PDU and its associations is most important in dementia care. Although the instrument used for measuring appropriateness of PDU needs to be developed specifically for this study, no other instruments known are suitable to investigate the appropriateness of PDU for NPS. However, it should be taken into account that the instruments’ assessment of appropriateness of PDU relies on medical files, which may be subjected to bad reporting. Yet, in our view this procedure is considered to be more objective than personal reports of ECPs.

Many of the instruments used for this study are well known in this field of research, and will contribute to giving clear insight in factors related to PDU, which can be used in improving nursing home patient care.

The mixed design of the study is another strength of this study, interviewing ECPs and nurses can reveal relevant factors that are not measured with quantitative instruments. So, this study not only gives insight into frequency and appropriateness of PDU, but also into a diversity of possible associations, which can be used in future quantitative research.

PROPER I will provide insight in associations of (appropriateness of) PDU and thus the barriers of optimal prescription, which is the first step towards safer PDU.

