### Nurse factors

Experienced organizational culture will be measured with the Competing Values Framework Scale (CVFS) [42], the validated Dutch version [43], a 6-item scale where four phrases need to be set in an order of personal relevance. The CVFS assesses the 6 dimensions of the competing values framework [44]: dominant organizational characteristic, administration, management style, organizational glue, strategic emphasis and criteria for success.

Workload will be assessed with a workload questionnaire ‘werkdruklijst’ developed by De Jonge [45,46]. This scale consist of 10 items about unit workload, each item can be scored on a five-point Likert scale.

Situations, feelings and thoughts about dementia care will also be administered, with a 29-item scale, which will be published as the Strain in dementia Care (SDC) scale ([name] and [name], personal communication 2013). There’s a four-point Likert scale for each item, also a score on another four-point Likert scale can be given for professional caregiver burden related to the item. Higher scores indicate high workload.

Job satisfaction will be measured with the Maastricht Work Satisfaction Scale for Healthcare (MAS-GZ) [47]; a 21-item, five-point Likert scale that focuses on nursing staff satisfaction. It consist of seven subscales with three items each about satisfaction with: quality of care, opportunities of self-actualization/growth, supervisor, possibilities for promotion, clarity of tasks and rules, contact with colleagues and contact with patients.

‘Attitude to dementia care’ will be measured by the ADQ (see physician level) [41].

Information about demographic characteristics of the nurse will be collected: age, sex, educational level, work experience, number of years since education.

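### Appropriateness is scored from medical files alone, so if charting varies with workload or distress, an effect on documentation cannot be separated from one on prescribing

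*Protocol article*

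**What the plan says.** Under the primary-outcome heading the article plans to adapt the Medication Appropriateness Index and "develop an instrument that screens medical files for appropriateness of psychotropic drug prescription in dementia". The reference material is a guideline, a pharmacy database and a national formulary. Of the database it says: "The instrument will also include information about interactions and contraindications that originates from the database". These sources supply standards for drugs, not a second account of the patient. On scoring it says: "Items will be weighted by an expert panel of pharmacists and ECPs". Table 1 has researchers completing the tool and lists the instrument as not yet announced.

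Workload is measured by nurse questionnaire (Nurse factors: "This scale consist of 10 items about unit workload"), as is strain in dementia care. No workload measure for the physician is listed.

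The Discussion sets out the general hypothesis ("It is hypothesized that the frequency as well as appropriateness of PDU varies between DSCUs", through patient, physician, nurse and environmental factors) and then the specific expectation: "it is expected that factors like workload and staff distress influence the appropriateness of PDU". It accepts that the assessment "relies on medical files, which may be subjected to bad reporting", and answers that "in our view this procedure is considered to be more objective than personal reports of ECPs". Data analysis describes a multilevel model that allows for nesting in units.

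**The concern.** The file is the only patient-level source shown for the appropriateness score. The admitted weakness is presented as a general limitation, but for one stated expectation it may not be neutral. Units with high workload or distress might also keep poorer records. The measurement error would then differ by exposure, and an association between workload and scored appropriateness could arise with identical prescribing on every unit, or a real one could be hidden.

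The defence in the Discussion compares files with physicians' own reports. It does not ask whether file quality varies with the factors being tested. The article closes by promising insight into barriers to optimal prescription. A workload association reported in those terms might instead describe a barrier to record-keeping.

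**Working it through.** **What the article supplies.** It gives no figure for documentation quality or for the rate of inappropriate prescribing. The sample-size figures set the scale: 360 / 0.67 = 537.3, rounded up to 538, close to the stated 540; 36 units x 15 patients = 540. Expected users are 540 x 0.67 = 361.8, about 360, so 10 per unit and 180 in each half if units are split by workload.

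**What is assumed.** True inappropriateness p = 30% on all units. Proportion undocumented m = 10% on low-workload units and 25% or 30% on high-workload units. There is no true effect of workload on prescribing.

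**Undocumented counted fully as inappropriate.** Observed rate = p + (1 - p)m.
- Low: 0.30 + 0.70 x 0.10 = 0.37
- High, m = 25%: 0.30 + 0.70 x 0.25 = 0.475, difference +10.5 points
- High, m = 30%: 0.30 + 0.70 x 0.30 = 0.51, difference +14 points, odds ratio (0.51/0.49)/(0.37/0.63) = 1.77

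**Undocumented not flagged.** Observed rate = p(1 - m).
- Low: 0.30 x 0.90 = 0.27
- High, m = 25%: 0.30 x 0.75 = 0.225, difference -4.5 points
- High, m = 30%: 0.30 x 0.70 = 0.21, difference -6 points, odds ratio (0.21/0.79)/(0.27/0.73) = 0.72

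**Equal charting.** With m = 10% on both, the difference is 0 and the odds ratio 1.00 under either rule.

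**Weighted items.** If a missing entry adds only a fraction w (below 1) of a full inappropriate rating, the first rule gives a difference of w(1 - p)(m_high - m_low). It shrinks in proportion to w.

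**Wider range.** Take p = 30% or 50% and m = 10% v 20%, 10% v 30% or 20% v 30%. The spurious odds ratio is 1.23 to 1.77 under the first rule and 0.66 to 0.85 under the second.

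**Does the multilevel model help?** No. The shift in expected score is a function of the exposure, so it enters the workload coefficient. A unit random effect absorbs unit variation unrelated to workload and corrects the standard error. It does not remove an error that follows workload.

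**How often it would look significant.** This is a two-group approximation at two-sided 5%, under the first rule, with 180 users per half and design effect 1 + (10 - 1) x ICC, that is 1, 1.45 and 1.9 for ICC 0, 0.05 and 0.10.

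| p; m low v high | Observed | ICC 0 | ICC 0.05 | ICC 0.10 |
|---|---|---|---|---|
| 30%; 10% v 30% | 37% v 51% | 0.77 | 0.60 | 0.49 |
| 30%; 10% v 20% | 37% v 44% | 0.27 | 0.20 | 0.16 |
| 50%; 10% v 20% | 55% v 60% | 0.16 | 0.12 | 0.10 |

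The planned model is richer than this comparison, so these values give an order of magnitude only.

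**The case against.** The strongest reply is that much of the chain is not in the article. Nothing says how an undocumented item is scored, and item codes are details that an article may leave to the full protocol or the instrument description. A reader might infer that poor charting will be counted as inappropriate prescribing. The text does not say so, and the bias reverses under the other rule. Nor does it say that busy units chart worse or who writes the files; workload is rated by nurses. Because items are weighted, one missing entry need not change the rating of a drug.

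Two further inferences are unsupported. Workload and distress are not the main hypothesis; they are one expectation within a hypothesis covering four groups of factors. And the follow-on PROPER II trial would not be aimed at the wrong target: Design and eligibility already describes its intervention, a structured drug review rather than a workload measure.

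Finally, the reliance on files is disclosed, and the staff interviews may help interpretation.

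All of this limits the size and certainty of the point. What stands does not depend on the missing scoring rule, since either rule distorts the association if charting varies with workload. Disclosing bad reporting in general does not cover error that follows the exposure, and interviews will not quantify it.

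**Conclusion.** The point holds as a conditional threat to the interpretation of one primary outcome. A single file-based source, an admitted reporting weakness and an expectation about workload and distress stand in one article without being connected, and the analysis described cannot separate documentation from prescribing.

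The condition is that charting quality varies with workload or distress, which is plausible and unproven. On the main assumed figures the spurious difference runs from about -6 to +14 points according to the scoring rule. It is smaller with weighting and zero if charting is equal. The frequency outcome is not affected by this scoring. It would go too far to say that the workload association is bound to be spurious or that its direction is known.

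**What to change.** While the instrument is still to be developed:

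1. Give each item a code 'not documented', distinct from 'documented and inappropriate'.
2. Model the proportion of items not documented against the same factors, in the same multilevel framework.
3. Report that result beside the combined score and the score from documented items only. State that the last is conditional on documentation and may be selected if documentation depends on both workload and prescribing quality. For that reason it should not serve alone as the test of an effect on prescribing.
4. Describe a workload or distress association as a barrier to optimal prescription only if the three results together do not point to documentation as the explanation.
5. Add to the Discussion that bad reporting may differ by workload or distress.

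The cost is one extra code and one extra model, with no new data source. The documented-only analysis has fewer scorable items and so less precision.
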